## Discussion

Schizophrenia is a debilitating condition with a severe impact on quality of life, high rates of relapse, and low employment rates, between 10 and 20% in Europe. The total cost in France in 2005 amounted to €3795 million. Fatigue is highly prevalent in schizophrenia and constitutes a significant barrier to employment, social interactions, and quality of life and is likely to have negative impacts on medical comorbidities by constituting an important barrier to physical activity.

However, and surprisingly, certainly because of the overlap between depression and negative symptoms, fatigue is considered to be resistant to psychological and pharmacological interventions and is a neglected phenomenon in clinical care of individuals with schizophrenia. Interventions for fatigue have been shown to be effective for numerous other medical conditions with or without cognitive deficits but have never been studied in schizophrenia.

Our project is to propose the first randomized controlled study designed to alleviate fatigue severity in schizophrenia, which could lead to direct short-term improvements of quality of life, affective state, autonomy, and motivation and at long-term reduction of cardiovascular risk factors and morbidity. In addition, the expected benefit for patients is to produce an integrative model, taking into account psychological and biological factors, in order to better understand and support fatigue in schizophrenia.

### Ethical considerations and confidentiality

There are to our knowledge no potential risks involved with participating in the intervention proposed in this study other than the usual risk linked to moderate walking.

Risks concerning the collection of blood samples were weak: unease, bruise, or anxiety.

Risks concerning neuropsychological and clinical evaluations are weak: anxiety, tension, and tiredness.

Regarding the vigilance of the project which are responsibilities of the investigator and sponsor, the reporting of serious adverse events (sAE) and annual safety reports will be monitored and carried out in accordance with regulations.

#### Collection of AEs

AEs will be collected non-systematically through spontaneous report by participants or other members of the team. Complete and appropriate data on all AEs experienced during the clinical trial will be recorded on the AE form of the CRF on an ongoing basis for the duration of the study. Each AE report shall include a description of the event, an assessment of its seriousness, its duration, intensity, relationship to the study medication, other causality factors (if any), any concomitant medication dispensed, actions taken with the study drug or other therapeutic interventions, and outcome at the end of the observation period. For each AE, a separate AE form will be filled out.

All AEs (whether expected or unexpected) will be recorded in the eCRF and will be reported in the subsequent trial publications except for the following:
Admission for social or administrative reasonsHospitalization predefined by the protocolHospitalization for scheduled medical or surgical treatment prior to research

AEs will be followed up until their resolution or stabilization. However, the observation period will be cut off after the last patient has finished his final visit (LPLV).

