### Intervention description

#### Experimental group

Treatment as usual (see below)ENERGY intervention:
Fourteen sessions of 1-h CBT interventionOne session per weekWith a psychologist (different to the psychologist who will perform the assessments)Individual sessions

ENERGY intervention is a cognitive-behavioral intervention developed by Knoop and Bleijenberg [24] and adapted in French by Cantin and colleagues [25]. The ENERGY intervention will be delivered according to a standardized treatment manual comprising six modules addressing fatigue and sleep over 14 individual therapy sessions (Table 1). The treatment encompasses the core CBT principles of psycho-education, behavioral activation, behavioral experiments, cognitive restructuring, problem-solving, and relapse prevention [26]. Sessions will follow the traditional CBT structure of agenda setting, review of homework tasks, and introduction of a new concept/technique with collaborative discussion on how to implement such strategies in the participant’s day-to-day environment [26].

**Table 1 Tab1:** Treatment modules and therapeutic aims

Module	Content summary	Aims
1	Psychoeducation CBT Framework	Shift unhelpful beliefs around symptoms Encourage understanding of link between activity levels and sleep habits with syndrome maintenance
2	Reorganize daily schedules	Initiate pacing of tasks, with optimal number of rest breaks Increase hygiene practices
3	Energy conservation	Integrate meaningful activities depending on goals and available energy
4	Cognitive restructuring Sleep interventions	Modify rest and sleep appraisals Stimulus control, bedtime restriction, hypersomnia management Relaxation
5	Strategies for physical and mental fatigue	Environmental modification, restructuring tasks Cognitive strategies for information processing, attention and time pressure management
6	Review techniques Relapse prevention	Consolidate treatment gains

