#### Control group

Treatment as usual comprises antipsychotic medication, day hospital, and ambulatory care during all the study.

Concomitant care: no concomitant care is prohibited during the trial.

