If a patient misses their appointment, the psychologist will call him/her. All attempts will be documented in the patient’s medical records. In case of discontinuation, the investigator will perform all examinations scheduled for the final study visit, which includes recording of AEs. In any case, the patient will be treated in accordance with standard care in the center.

Investigators should make every effort to minimize the number of patients lost to follow-up and to obtain a maximum of information on patients lost to follow-up, particularly in the search for any AEs.

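### Spontaneous-only routine AE collection, combined with 14 extra individual sessions in the ENERGY arm, leaves non-serious AE counts by arm liable to unequal ascertainment

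*Protocol article*

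**What the plan says.** All references are to the protocol article.

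- **Collection rule** (Collection of AEs): "AEs will be collected non-systematically through spontaneous report by participants or other members of the team".
- **Completeness promised in the same section:** "Complete and appropriate data on all AEs experienced during the clinical trial will be recorded on the AE form of the CRF". With three listed kinds of admission excepted, AEs "will be recorded in the eCRF and will be reported in the subsequent trial publications".
- **ENERGY arm** (Experimental group): this arm is listed as "Treatment as usual (see below)ENERGY intervention", that is, usual care plus the therapy. The therapy is 14 weekly one-hour contacts, described as "Individual sessions", with a psychologist who is not the assessor.
- **TAU arm** (Control group): "Treatment as usual comprises antipsychotic medication, day hospital, and ambulatory care during all the study".
- **AE recording outside the spontaneous route** (Data collection): "In case of discontinuation, the investigator will perform all examinations scheduled for the final study visit, which includes recording of AEs". The same section asks investigators to look for AEs in patients lost to follow-up.
- **SAEs** (Notification of SAEs): these have their own reporting duty to the sponsor and must be entered in the CRF.

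The section on statistical analysis describes no between-arm test of AEs. A safety set is mentioned under Trial withdrawal or discontinuation.

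**The concern.** When AEs are recorded only if somebody volunteers them, the count depends on how often patients speak to someone who can record or pass on an event. Here that opportunity differs by arm by design. For about three months, ENERGY patients meet a trial therapist once a week on top of usual care. TAU patients have no counterpart. The therapist also knows the allocation and is listening for problems with sleep, activity and fatigue.

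The section also sits uneasily with itself: a method that it calls non-systematic is expected to yield complete data on all events.

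At stake is how the promised AE listing will be read. Even without a planned test, readers will set the two columns side by side. A higher ENERGY column could reflect harm, more listening, or both, and no later analysis can recover events that were never elicited in the TAU arm. There is no data safety monitoring board, so the AE record carries more of the weight in judging tolerability.

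**Working it through.** The document gives no AE rate, no reporting probability and no AE comparison, so there is no stated figure to reproduce. The check has two parts.

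**1. Is reporting opportunity equal by design?**

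| Route for an AE to be recorded | ENERGY | TAU |
|---|---|---|
| Day hospital and ambulatory care | yes | yes |
| 3- and 9-month visits | yes | yes |
| AE recording at the final visit | yes | yes |
| AE search if lost to follow-up | yes | yes |
| 14 one-hour sessions with a trial therapist | yes | no |

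Four routes are shared and one is not. The unshared route falls in the treatment period. After the 3-month visit, planned contact is the same in both arms. None of the shared routes is described as a standard question put to everyone on a common schedule.

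**2. What does a difference in capture do to the counts?**

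Let r be the true risk of at least one non-serious AE, equal in both arms, and let c be the probability that such an AE is captured.

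- Recorded proportion = r × c
- Recorded risk ratio = (r × c_ENERGY) / (r × c_TAU) = c_ENERGY / c_TAU
- Recorded risk difference = r × (c_ENERGY − c_TAU)

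So any ratio in capture passes unchanged into the recorded risk ratio. With assumed values r = 30% and c_TAU = 50%:

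| c_ENERGY | TAU recorded | ENERGY recorded | Ratio |
|---|---|---|---|
| 50% | 0.30 × 0.50 = 15% | 0.30 × 0.50 = 15% | 1.00 |
| 60% | 15% | 0.30 × 0.60 = 18% | 1.20 |
| 70% | 15% | 0.30 × 0.70 = 21% | 1.40 |
| 80% | 15% | 0.30 × 0.80 = 24% | 1.60 |

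With the planned 100 patients per group, that is 15 patients against 18 to 24.

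Over a wider assumed range (r from 10% to 50%, c_TAU from 30% to 70%, gap of 10 to 30 percentage points):

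- the ratio runs from 0.80/0.70 = 1.14 to 0.60/0.30 = 2.00;
- the difference runs from 0.10 × 0.10 = 1 point to 0.50 × 0.30 = 15 points.

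Every value of r and c here is an assumption. The table shows the mechanism and does not estimate the bias in this trial. Because no AE test is planned, I have not turned these figures into error rates.

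**The case against.** The case on the other side is substantial, and most of it limits the point without removing it.

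- **Collection is not wholly spontaneous.** The document mentions AE recording at the final visit and an AE search in patients lost to follow-up, for both arms. This stands, and it narrows the gap. Neither is described as the same structured question asked of everyone.
- **Usual care gives frequent contact in both arms.** This also stands. A reader might count trial contacts, 14 sessions plus 2 visits against 2 visits, and infer a very large distortion. With a chance q per contact that an AE is recorded, 1 − (1 − q)^16 against 1 − (1 − q)^2 at q = 0.05 gives 56% against 10%. The document does not support that reading. The formula contains no true event rate, q is invented, and day-hospital contact is left out. Adding an assumed 39 weekly day-hospital contacts to each arm gives 1 − 0.95^55 = 94% against 1 − 0.95^41 = 88%.
- **Serious events have a separate duty.** Immediate reporting applies to SAEs, and those exempt from it, such as hospitalizations, are still documented. Their detection should depend little on therapy sessions.
- **Some plausible harms are measured anyway.** Psychotic symptoms, depression, hypersomnolence and insomnia are scored at baseline, 3 and 9 months in both arms, with blinded assessors. Worsening there would show without being volunteered. Other non-serious events have no such cover.
- **No between-arm AE test is planned.** This is correct. The point therefore concerns how the published counts can be read and does not touch any specified analysis.

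A reader might also take the ethics section's statement that the authors know of no potential risk beyond moderate walking as a claim that these data must support. It is a judgement made before the trial. Extra recording in ENERGY would in any case make the therapy look riskier, not safer.

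**Conclusion.** The point holds in a limited form. A collection rule that is explicitly non-systematic, combined with an extra reporting route in one arm only, leaves the published non-serious AE counts liable to unequal ascertainment, most likely inflating the ENERGY arm.

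The direction is an inference from the therapist being an added reporter on top of shared usual care. The size is unknown: the ratios of 1.20 to 1.60, and of 1.14 to 2.00 over the wider range, rest entirely on assumed capture probabilities.

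It would go too far to say that the harms comparison is shown to be biased, that the AE data cannot be interpreted, or that all harms are affected. SAE reporting duties, the sample size and the efficacy analyses are untouched. The change is worth making because it is cheap and because the gap cannot be repaired after data collection.

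**What to change.** Amend Collection of AEs as follows.

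1. At the existing 3- and 9-month visits, every participant in both arms is asked the same open question about AEs since the previous visit.
2. The question is asked by the physician who already follows the patient, not by the assessing psychologist. An answer can easily reveal that the patient had therapy, and the assessor is meant to stay blind.
3. Spontaneous reports continue to be recorded.
4. The eCRF records the source of each AE: visit question, therapy session, day hospital or other.
5. AEs are tabulated by arm both overall and by source. The visit-elicited events then give a like-for-like comparison beside the total.

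The visit-elicited events should accompany the total and not replace it. Recall over three to six months is imperfect, and the document itself notes that memory deficits are common in this population.

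The cost is one eCRF item and a few minutes at each of two visits that already take place. AE counts will rise somewhat in both arms.

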#### Notification of SAEs

All SAEs occurring during the study must be reported on the SAE form to the Pharmacovigilance Clinical Trial Department of CHU Montpellier handling pharmacovigilance matters in this study on behalf of the sponsor.

The Pharmacovigilance Clinical Trial Department of the sponsor must be informed immediately (i.e., within 24 h) of the occurrence of any SAE by fax or by e-mail.

The investigator is required to include any investigations as may be indicated to elucidate the nature or the causality of the SAE. This may include additional lab tests, histopathological examinations, and consultations with other healthcare professional or if the patient dies, any post mortem findings. The relation between the event and the study drugs should be evaluated by the investigator.

After the initial report, the investigator is required to follow each patient until the end of the SAE and to provide further information on the patient’s condition to the sponsor. The investigator must also record all SAEs in the CRF.

Some serious adverse events that do not require immediate reporting will only be documented on the CRF/source data such as:
Serious adverse events occurring after given informed consents, but before starting study procedures/application of study medicationHospitalizations

### Trial withdrawal or discontinuation

Study participation is voluntary. The subjects have the right to withdraw their consent from the study at any time and for any reason, without jeopardizing their medical care. The investigator also has the right to withdraw patients in agreement with the sponsor or his delegate. The investigator has the right to withdraw subjects from the trial in the event of concurrent illness, adverse events, and treatment failure after a prescribed procedure, protocol violations, and other reasons.

Subjects must be withdrawn from the study under the following circumstances:
The subject withdraws consent.Development of another illness or condition which would interfere with the subject’s continued participation.Discovery that the subject entered the clinical trial in violation of the protocol or occurrence of a significant protocol violation during the clinical trial.Any situation that in the opinion of the investigator would pose inacceptable risks to the subject if trial participation is continued.

For any discontinuation, the investigator should obtain all required details and should document the date and reason of the premature termination in the CRF.

If the reason for withdrawal is an AE, the specific event will be recorded in the CRF. The investigator will make thorough efforts to document the outcome.

Patients prematurely withdrawn or lost to follow-up will be analyzed at least in the safety set and in the conditions of confidentiality.

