## Methods: data collection, management, and analysis

### Data collection

Several scales and tests used in this study are comprised within the standardized evaluations performed in the schizophrenia expert centers and are therefore already used on a daily basis in the centers implicated in the study. Each year, all the members of the centers attend quotation sessions in order to ensure inter-rater validity.

For the scales specific to this study (MFI, CAINS, IMI-SR, IHSS, BQ, SCI, IPAQ), we will organize training sessions before the beginning of the protocol in the French expert schizophrenia Network. In addition, all schizophrenia expert centers meet monthly in Créteil, in a meeting organized by the FondaMental Foundation and have specific expertise in clinical, neuropsychological, and biological evaluation in schizophrenia. All teams will be trained in the intervention the year before the beginning of the study to guarantee the homogeneity and quality of treatment across the centers.

Data will be collected or reported in an electronic case report form (e-CRF) developed using the software Capture System EnnovClinical to control for data quality at entry. The connection is via a username and password unique to each specific user and giving access only to the data of the centers’ user. An audit trail function is included allowing a supervision and traceability of all actions from all users.

Concerning biological evaluations, we will have access to specialized platforms for Microbial translocation and inflammatory and immunologic dosing, localized in Nîmes and Montpellier allowing great communication with the study coordinator based in Montpellier.

Once a participant has been enrolled and randomized into their study arm, the study site will put in place every effort to follow the participant throughout the course of the study. In order to improve adherence and prevent loss to follow-up, we will organize phone calls and/or emails that will be sent before the intervention to recall patients of their appointments. Patients will be already following day hospital care, which we believe will also increase adherence to the study. Furthermore, each evaluation will be planned in accordance with each patients’ schedule, and all patients will be phoned 24 h before their evaluation to remind them of their appointment.

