### Statistical analysis

The statistical analysis plan (SAP), covering all the analyses to be performed on all data, will be written before database lock for final extraction.

For all collected variables, descriptive statistics will be shown for both study arms in order to verify the initial comparability of the groups. For metric variables, a check as to whether the data can be assumed to be normally distributed will be first conducted. For normally distributed variables, means and standard deviations will be calculated, whereas for skewed variables, medians and ranges will be given. For categorical variables group proportions and contingency tables will be prepared.

All tests of efficacy will be conducted on an intentions to treat (ITT) basis using, in case of missing data, the Last Observation Carried Forward method, and/or multiple or mean imputation [50]. A per protocol sensitivity analysis will also be performed taking into account only patients who completed the whole study without any major protocol deviations. This will enable us to reinforce the stability of results obtained by ITT approach.

Significance level will be set at *p* < 0.05. All statistical analyses will be performed using SAS software (SAS Institute, Cary, NC, USA).

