#### Main endpoint analysis

The efficacy of the ENERGY intervention will be studied firstly by comparing the change in fatigue score (using the scores on the MFI) between inclusion/randomization and the 9-month follow-up (primary outcome) in the intervention group compared to the TAU group.

For each subject, the relative difference (delta) between the inclusion and 9-month fatigue score will be calculated. The normality of the delta score will be tested using the Shapiro Wilk’s test. If the distribution is skewed a transformation will be performed to normalize it.

Study arms will be compared between inclusion scores and the 9-month scores using mean differences. These comparisons will be done using Student’s *T* test and general linear regression models adjusting for covariates. Socio-demographic and clinical variables will be tested as potential confounders using general linear regression models, with the *p* value set at 0.10.

A second analysis will be carried out with the general fatigue score as the outcome variable, adjusting for general fatigue score at inclusion.

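### Patients can, and in some cases must, be withdrawn from the trial rather than only from therapy for treatment failure, protocol violations or ineligible entry, which creates avoidable gaps in the 9-month MFI

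*Protocol article*

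**What the plan says.** Under Trial withdrawal or discontinuation, the investigator may remove patients with the agreement of the sponsor or its delegate. The investigator may "withdraw subjects from the trial in the event of concurrent illness, adverse events, and treatment failure after a prescribed procedure, protocol violations", among other reasons. The same section lists compulsory withdrawals from the study, including "Discovery that the subject entered the clinical trial in violation of the protocol or occurrence of a significant protocol violation during the clinical trial". A separate compulsory ground covers unacceptable risk to the patient. On analysis, the section says only that "Patients prematurely withdrawn or lost to follow-up will be analyzed at least in the safety set".

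Other sections bear on the same patients:

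- Main endpoint analysis: "For each subject, the relative difference (delta) between the inclusion and 9-month fatigue score will be calculated".
- Data collection, on retention: "the study site will put in place every effort to follow the participant throughout the course of the study".
- Data collection, on leaving: "In case of discontinuation, the investigator will perform all examinations scheduled for the final study visit".
- Statistical analysis: all efficacy tests are ITT, using, "in case of missing data, the Last Observation Carried Forward method, and/or multiple or mean imputation". A per-protocol sensitivity analysis is added, "taking into account only patients who completed the whole study without any major protocol deviations".

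**The concern.** The withdrawal clause speaks of the trial and the study. It never separates stopping the ENERGY sessions from stopping follow-up. Four of its grounds are treatment failure, discretionary removal for protocol violations, compulsory removal for a significant violation, and compulsory removal for ineligible entry. In none of them has the patient refused further assessment or become unable to fill in a self-report questionnaire.

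The primary endpoint is the change in MFI to 9 months, about 6 months after therapy ends. A patient withdrawn earlier has no such score. This is a rule of conduct, not an analysis detail left for later: an analysis plan can choose how to impute, but it cannot recover a score that was never collected.

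The rule also works against two of the protocol's own aims, which are to follow every randomised patient and to analyse by ITT. It is not needed to deal with deviators, because the per-protocol analysis already sets them aside. Treatment failure matters most, since those patients are by definition doing poorly and their missing scores relate to the outcome.

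**Working it through.** **1. The plan's own figure.** The sample size section assumes a 2-point difference on the general fatigue subscale and an SD of 4, and gives 73 per group. A two-sided two-sample t-test at alpha 0.05 and power 0.85 (printed as .085) needs 72.8, so 73 is reproduced. With 100 recruited per arm, 73 remain after 27% loss. The planned loss of 15–20% needs 73/0.85 = 86 or 73/0.80 = 92 per arm. Power is therefore not the issue; bias is.

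**2. Which grounds prevent a 9-month score?**

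| Ground | Rules out a 9-month MFI? | Outcome-related by definition? |
|---|---|---|
| Treatment failure | No | Yes |
| Protocol violations (discretionary) | No | No |
| Significant violation (compulsory) | No | No |
| Ineligible entry (compulsory) | No | No; fixed at baseline |

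**3. Possible size.** The documents give no withdrawal rates for these grounds, so every rate below is an assumption.

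Let X be the change in score at exit and Y the change at 9 months. Both have the same mean and an SD of 4, with correlation r. The SD of change is 4 × √(2(1 − ρ)), which is 4.0 for an inclusion-to-9-month correlation ρ of 0.5. The worst fraction p on X is withdrawn, in ENERGY only. Write z for the normal quantile at 1 − p and φ for the normal density.

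- Arm-mean imputation: shift towards ENERGY = r × 4 × φ(z)/(1 − p).
- Exit score carried forward: shift against ENERGY = (1 − r) × 4 × φ(z).

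Example with p = 0.10 and r = 0.5, where φ(z) = 0.1755: 0.5 × 4 × 0.1755/0.90 = 0.39, and 0.5 × 4 × 0.1755 = 0.35.

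| p | Arm mean, r = 0.5 | Carried forward, r = 0.5 |
|---|---|---|
| 2% | 0.10 | 0.10 |
| 5% | 0.22 | 0.21 |
| 10% | 0.39 | 0.35 |
| 15% | 0.55 | 0.47 |

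**4. Sensitivity.**

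- **Correlation**, p from 2% to 15%. At r = 0.3, arm-mean shifts are 0.06–0.33 and carried-forward shifts 0.14–0.65. At r = 0.7 they are 0.14–0.77 and 0.06–0.28.
- **TAU withdrawn at half the ENERGY rate**, r = 0.5: 0.05, 0.10, 0.17, 0.24 (arm mean) and 0.04, 0.09, 0.15, 0.18 (carried forward).
- **Equal rates and equal selection in both arms:** zero. More withdrawal in TAU reverses the signs.
- **Withdrawal at random within the worse half**, ENERGY only, r = 0.5: 0.03, 0.08, 0.18, 0.28 (arm mean) and 0.03, 0.08, 0.16, 0.24 (carried forward). This is about half the table's figures or less.
- **Multiple imputation using the exit score:** about zero if withdrawal depends only on that score.
- **p = 20%**, the top of the protocol's all-cause loss range, r = 0.5: 0.5 × 4 × 0.280/0.80 = 0.70 and 0.5 × 4 × 0.280 = 0.56. This would need all of that loss to be of this kind and in one arm.
- **Smaller SD.** At ρ = 0.66, the lowest MFI test-retest correlation quoted under primary outcome measures, the SD of change is 3.3 and every figure shrinks by a factor of 0.82.

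**The case against.** The strongest reply is that the protocol already limits the damage, and much of that reply stands.

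- **Sponsor agreement.** Discretionary withdrawal needs the agreement of the sponsor or its delegate. This is a real check, but it does not apply to the compulsory grounds and does not preserve follow-up.
- **Exit examination.** The final-visit assessments are done at discontinuation, which should include an MFI. This helps, but nothing says it is taken at month 9 or that the 9-month visit still takes place.
- **ITT with imputation.** A reader might infer that withdrawn patients drop out of the efficacy analysis. The documents do not support that: the reference to the safety set is a minimum, and ITT with imputation applies to all efficacy tests. The tension is practical, not a formal contradiction.
- **Outcome-related gaps.** A reader might call all four grounds outcome-related. Only treatment failure is so by definition. Eligibility is checked before randomisation, so ineligible entry should not differ by arm.
- **Arm imbalance.** Only ENERGY adds 14 weekly sessions, which gives more to deviate from, and the investigator is not stated to be blind. But no section calls a missed session a violation, and delayed therapy is explicitly tolerated. Imbalance is possible, not shown.
- **Per-protocol analysis.** A reader might think this analysis suffers most. It excludes major deviators whether or not they are withdrawn, so that is not established.
- **The model.** Equal means at exit and at 9 months are doubtful for someone leaving mid-therapy, and strict removal of the worst patients is extreme. The figures show scale only.
- **Boilerplate.** The clause may be generic text. It still binds sites as written.

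**Conclusion.** The point holds as an avoidable design weakness. As written, the clause removes patients from follow-up on grounds that do not stop them giving a 9-month MFI, and neither the exit examination nor imputation replaces that score.

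The size and direction of any bias are unknown, because they depend on withdrawal rates by arm and on which imputation option is used. With an SD of change of 4, ENERGY-only withdrawal of the worst 2–15% at exit, and r from 0.3 to 0.7, the ITT difference shifts by about 0.06 to 0.8 points in favour of ENERGY (arm mean) or about 0.06 to 0.65 points against it (exit score carried forward), compared with a planned effect of 2. Softer selection gives about half of this or less, and some plausible settings give about zero.

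It is tempting to infer that the rule biases the trial in favour of ENERGY. That follows if non-improvers leave ENERGY and their baseline is carried forward, but the exit examination supplies a later score, and carrying that forward reverses the sign in this model. The documents do not settle the direction. The change is worth making because it is simple and the lost data cannot be recovered.

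**What to change.** In the section on trial withdrawal or discontinuation, remove treatment failure, protocol violations (discretionary or significant) and ineligible entry as grounds for leaving the trial. Make them reasons to stop therapy if clinically indicated, or recorded deviations handled in the per-protocol set. Keep the unacceptable-risk ground, so no protection is lost.

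State there and under Data collection that:

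- stopping the ENERGY sessions is not withdrawal from the trial;
- both arms keep the 3- and 9-month assessments unless the patient withdraws consent to follow-up;
- any examination at discontinuation is additional to the 9-month visit.

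The cost is a protocol amendment, with the steering committee and ethics approvals described under Trial governance and monitoring, plus some extra follow-up work at sites. That work is in line with the retention effort the protocol already promises. No sample-size figure changes.
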